### Procedure

After the Research Committee of the Andalusian School of Public Health had approved the trial, each patient was contacted in consecutive order. To facilitate recruitment, electronic medical records were searched for potentially eligible patients. During routine clinic visits they informed their patients of the study and invited them to participate. The study objectives were explained to the patient, who was then asked to sign the informed consent form. If a patient declined to participate, the next patient attending an appointment was asked to participate. If patients agreed to participate they completed a questionnaire to collect their socio-demographic characteristics, had a blood draw and were asked to return 14 days later to begin the intervention (see Figure 1).

**Figure 1 F1:**
[figure not shown]
Study procedure.

### Interventions

The GPs interested in participating were assigned randomization to one of three intervention statuses: face-to face, face-to-face intervention plus telephone reinforcement and control group.

#### Intervention A

(face-to-face intervention) is carried out by the GPs during the clinic visit and consists of seven visits, one every three months. Each session consists of completing a diabetes care record sheet (DCRS) together with the patient. The DCRS consists of two parts: Five questions on self-care activities in the last three months and a graph with previously measured HbA1c levels (see Figure 2). This information is completed at each session, resulting in a graph showing the evolution of glycaemic control related to self-care activities. The DCRS is explained patients, emphasising the relationship between self-care and glycemic control. At the end of the session, patients are given a copy of the DCRS and suggested to show it and discuss it with their relatives.

**Figure 2 F2:**
[figure not shown]
Diabetes care record sheet (DCRS).

To standardise the intervention style, the nine general practitioners were trained in cognitive, emotional and communication aspects. In addition, every six months a joint meeting was held with the researchers and doctors to address complications, go over the intervention process and ensure standardisation of the interventions.

#### Intervention B

(face-to-face intervention plus telephone reinforcement) In this group patients receive the above described intervention A plus a telephone reinforcement It consists of five telephone calls lasting about 10 minutes each, to provide advice on carrying out physical exercise and eating a balanced diet and to encourage the use of health services related to diabetes control. Any problems or doubts that patients have stemming from any aspect of diabetes care are also discussed. Telephone reinforcement is carried out by a professional who has previously been trained in promoting T2DM self-management and in motivational interviewing techniques.

#### Control group

Patients pertaining to this group receive minimal intervention, which consists in establishing a rigorous follow-up every three months, including a measurement of HbA1c. Since patients who meet the selection criteria are being seen every three months for routine diabetes monitoring, it was decided to schedule all study phases (recruitment, baseline measurements, interventions and final measurements) to be carried out at the routine three-monthly appointments. This minimises the human and economic cost of the study as well as the burden on patients, and, in turn, will reduce withdraw rates. Therefore, after recruitment patients are given an appointment every three months for a period of 15 months (five appointments in total).

### Evaluation of effectiveness

Intervention effectiveness will be measured as the proportion of patients who achieve adequate glycaemic control (HbA1c of less than 7%) by the end of the study.

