**Methods/Design:**

The study is being conducted in a General Practice located in a deprived neighbourhood of Granada, Spain. Diabetic patients 18 years old or older with a low educational level and inadequate glycaemic control (HbA1c > 7%) were recruited. General Practitioners (GPs) were randomised to three groups: intervention A, intervention B and control group. GPs allocated to intervention groups A and B received training in communication skills and are providing graphic feedback about glycosylated haemoglobin levels. Patients whose GPs were allocated to group B are additionally receiving telephone reinforcement whereas patients from the control group are receiving usual care. The described interventions are being conducted during 7 consecutive medical visits which are scheduled every three months. The main outcome measure will be HbA1c; blood pressure, lipidemia, body mass index and waist circumference will be considered as secondary outcome measures. Statistical analysis to evaluate the effectiveness of the interventions will include multilevel regression analysis with three hierarchical levels: medical visit level, patient level and GP level.

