### Sample size

The power was calculated assuming that at the end of the intervention 10% of the control group and 30% of intervention groups A and B would achieve improved diabetes control (with HbA1c values falling to below 7%). In order to provide a level of confidence of 95%, a power to detect significant differences between groups A and B was 59.4%, while the power to detect differences between groups B and control was 57.9%.

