### Study variables

Our primary outcome is HbA1c, which is well established as a surrogate marker for the development of diabetes-specific complications. Secondary outcomes are blood pressure (systolic and diastolic values), lipidemia (triglycerides, high density lipoprotein and low density lipoprotein), body mass index and waist circumference. All of them are assessed at 3-monthly intervals. All clinical measures are collected at baseline, before each visit and 3 months after the final visit. Sociodemographic information were collected after obtaining informed consent and included age, gender, ethnicity, social support and number of children.

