### Effectiveness assessment

Given the hierarchical structure of the information, the analyses will be performed using a multilevel model with three hierarchical levels: measurement (level 1), individual (level 2) and medical (level 3). The same levels of hierarchy will be used in the bivariate analyses, but adding a single independent variable to the model. All analyses will be carried out on an intention-to-treat basis.

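### HbA1c is named the primary outcome, but effectiveness and power rest on the proportion below 7%, and nothing says which measure decides the trial

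*Protocol article*

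**What the plan says.** Four places in the protocol article bear on the decisive measure.

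- **Abstract, Methods/Design:** "The main outcome measure will be HbA1c".
- **Study variables:** "Our primary outcome is HbA1c, which is well established as a surrogate marker". The secondary outcomes listed there are blood pressure, lipids, body mass index and waist circumference, all assessed three-monthly. The proportion below 7% is not listed.
- **Evaluation of effectiveness:** "Intervention effectiveness will be measured as the proportion of patients who achieve adequate glycaemic control (HbA1c of less than 7" (per cent), judged at the end of the study.
- **Sample size:** power assumes that "10% of the control group and 30% of intervention groups A and B would achieve improved diabetes control", defined as HbA1c falling below 7%.

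The section Effectiveness assessment says that "analyses will be performed using a multilevel model with three hierarchical levels" (measurement, patient, doctor). It does not name the dependent variable.

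**The concern.** A difference in mean HbA1c and a difference in the proportion below 7% are different quantities, with different models and different power. A fall from 8.8% to 7.8% moves the mean and adds nothing to the proportion. A fall from 7.1% to 6.9% barely moves the mean and counts as a full success. One measure can favour an intervention while the other does not. Because the article does not say which decides, the choice could be made after the results are known.

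The choice also affects power. The article itself lists limited power among its limitations, and only 8 of the 9 GPs contributed baseline data. Baseline HbA1c also differs between arms, so a fixed cut at 7% asks for a larger fall in one arm than in another.

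**Working it through.** **Inputs.** Table 1 gives n = 92 (control), 37 (A) and 52 (B). Mean baseline HbA1c is 8.77% (SD 1.46) overall, 8.57% in control and 9.16% in B (p = 0.031). Sample size gives 10% versus 30% at 95% confidence, taken here as two-sided 5%. The article gives no ICC, no number of GPs per arm and no n behind its power figures.

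**1. The plan's own power figures.** The article states 57.9% for B versus control. The pooled two-proportion formula at 92 and 52 gives:
- pooled rate (9.2 + 15.6)/144 = 0.172
- SE under the null √(0.172 × 0.828 × (1/92 + 1/52)) = 0.0655
- SE under the alternative √(0.09/92 + 0.21/52) = 0.0708
- power Φ((0.20 − 1.96 × 0.0655)/0.0708) = 84%

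Other standard variants give 79% to 90%. A design effect of about 1.97 would bring 84% down to 57.9%, but none is stated. The article also says "a power to detect significant differences between groups A and B was 59.4" (per cent), although both arms are assumed at 30%, so there is no difference to detect. The stated figures therefore do not reproduce and are not used below.

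**2. Fall needed to count as a success.**
- Control: 8.57 − 7 = 1.57 points
- B: 9.16 − 7 = 2.16 points
- All patients: 8.77 − 7 = 1.77 points

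**3. The same effect on the continuous scale, assuming normality and equal SDs.** Shift d = z(0.30) − z(0.10) = −0.524 + 1.282 = 0.757 SD, or 0.757 × 1.46 = 1.1 HbA1c points. Power for means is approximately Φ(d/√(1/n₁ + 1/n₂) − 1.96).

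| Contrast, no clustering | Proportion | Mean |
|---|---|---|
| B vs control (52 vs 92) | 84% | Φ(0.757/0.1735 − 1.96) = 99% |
| A vs control (37 vs 92) | 77% | Φ(0.757/0.1947 − 1.96) = 97% |

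For 80% power, n per arm is 62 for the proportion and 28 for the mean. The information lost is 1 − 28/62 = 55%. The asymptotic efficiency φ(z)²/[p(1 − p)] is 0.34 where 10% lie below the cut and 0.58 where 30% do.

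**4. Clustering by GP.** Take m = 181/9 = 20.1 patients per GP, a = 28/62 = 0.452, and the same ICC ρ for both measures. Efficiency is [ρ + (1 − ρ)/m] / [ρ + (1 − ρ)/(m·a)].

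| Assumed ICC | Loss of information | Simulated power, proportion vs mean |
|---|---|---|
| 0.01 | 50% | 54% vs 84% |
| 0.02 | 46% | 51% vs 78% |
| 0.05 | 37% | 43% vs 63% |
| 0.10 | 27% | 34% vs 47% |

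The simulation used normal data, B versus control, an assumed 3 versus 3 GPs with 17 and 31 patients each, a GP-level t-test and 20,000 runs. The proportion has less power at every ICC tried.

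**5. Skewness.** A normal distribution with mean 8.77 and SD 1.46 would put Φ((7 − 8.77)/1.46) = 11% below 7%. Entry required HbA1c above 7%, so right skew is plausible. With a gamma shape and no clustering, the shift that turns 10% into 30% is smaller:

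| Assumed skewness | Shift | Unadjusted means, B / A vs control |
|---|---|---|
| 0.7 | 0.59 SD | 92% / 85% |
| 1.0 | 0.51 SD | 83% / 74% |

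At skewness 1.0 the unadjusted mean has no advantage over the proportion (84% and 77%). Adjusting for baseline at an assumed correlation of 0.5 multiplies the residual SD by √0.75 = 0.866 and gives 92% and 85%. No matching gain was computed for a baseline-adjusted proportion.

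**The case against.** The strongest defence is that there is one endpoint. HbA1c is the variable, the proportion below 7% is its summary, and the power statement uses that summary. Part of this stands. Only HbA1c carries the label primary, so a reader who infers that the article declares two primary outcomes goes beyond the text. But the article never joins the variable to the summary, and it schedules HbA1c three-monthly with measurement as a model level. The decisive measure remains open.

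Reaching 7% is also a legitimate target that mirrors the entry criterion, so preferring the mean is partly a matter of judgement. The Discussion adds that baseline differences will be taken into account in future analyses, which could soften the imbalance point. It does not say how, or for which measure.

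Several stronger readings are tempting, and the documents do not support them:
- **The cut discards most of the information.** This holds only at patient level under normality (55%). With clustering the loss is about half or less, and skewness can remove the advantage of unadjusted means.
- **The planned multilevel model is a model for continuous HbA1c.** No dependent variable is named, and a three-level model can be logistic.
- **A binary analysis with 8 GPs has no small-sample correction.** Bias-corrected sandwich estimators, between-within degrees of freedom, GP-level t-tests and permutation tests all exist. Few GPs is a difficulty for the linear model too.
- **The data are already in, so only wording changes.** The article describes an ongoing study.

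**Conclusion.** The inconsistency is in the text and does not depend on any calculation. The named primary outcome and the effectiveness criterion are different measures, the second is not placed among the secondary outcomes, and no rule says which prevails. It should be fixed before analysis.

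The efficiency argument supports choosing the continuous measure but is less certain. The loss is about half at patient level under normality without clustering, about 27% to 50% for ICCs of 0.10 to 0.01, and possibly nil for unadjusted means at skewness 1.0. The ICCs, the GPs per arm, the skewness and the baseline correlation are all assumptions. The unequal fall required, about 2.2 points in B against 1.6 in control, comes directly from Table 1 and counts against an unadjusted final proportion whatever the distribution.

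**What to change.** Before analysis, state one primary outcome with its metric and time point: continuous HbA1c at the final assessment, as the between-arm contrast adjusted for baseline HbA1c, from the three-level model. Name HbA1c as that model's dependent variable. Make the proportion below 7% a named secondary outcome. Align Sample size, Evaluation of effectiveness, Study variables and Effectiveness assessment, and restate power as a mean difference with the assumed SD, ICC and number of GPs.

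The time point cannot be fixed until the schedule is reconciled. The abstract and Intervention A give seven three-monthly visits, whereas Control group gives five appointments over 15 months. Study variables places the last measurement three months after the final visit.

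The cost is a documented, dated amendment to an ongoing trial and a restated power figure. No new measurements are needed, because HbA1c is already scheduled three-monthly in all arms. The change does not cure the small number of GPs, which limits either measure.

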### Study variables

Our primary outcome is HbA1c, which is well established as a surrogate marker for the development of diabetes-specific complications. Secondary outcomes are blood pressure (systolic and diastolic values), lipidemia (triglycerides, high density lipoprotein and low density lipoprotein), body mass index and waist circumference. All of them are assessed at 3-monthly intervals. All clinical measures are collected at baseline, before each visit and 3 months after the final visit. Sociodemographic information were collected after obtaining informed consent and included age, gender, ethnicity, social support and number of children.

### Measurement tools

Social support is measured by Blake and McKay’s questionnaire [19]. “About how many friends or intimate or close relatives do you have? (People with whom you are comfortable and can talk about everything that happens)”. This question assesses the number of people available referring to a specific situation of tangible help. The category “low social support” means that the responder has 0 or 1 person as tangible aid, while “high social support” refers to having 2 or more such people. Finally, comorbidity is measured by asking the patient if he/she has any other disease apart from T2DM.

### Effectiveness assessment

Given the hierarchical structure of the information, the analyses will be performed using a multilevel model with three hierarchical levels: measurement (level 1), individual (level 2) and medical (level 3). The same levels of hierarchy will be used in the bivariate analyses, but adding a single independent variable to the model. All analyses will be carried out on an intention-to-treat basis.

### Trial status: recruitment and baseline characteristics

Table 1 shows the results of the first (sociodemographic data) and second (clinical data) appointments. Whenever a patient who met the inclusion criteria (age 18 years, low education and inadequate glycemic control) came to visit, the GP asked if they would collaborate in the study. Of all, 16 of them decided not to participate.

**Table 1 T1:** Demographic and clinical characteristics of study subjects, by study group

		**All participants n =181 n (%)**	**Control group n = 92 n (%)**	**Intervention A n = 37 n (%)**	**Intervention B n = 52 n (%)**	**p**
Sex	Female	100 (54.3%)	44 (49.4%)	23 (63.9%)	31 (64.6%)	
	Male	80 (43.5%)	45 (50.6%)	13 (36.1%)	17 (35.4%)	0.143
Ethnicity	Caucasian	143 (80.8%)	77 (86.5%)	24 (66.7%)	36 (75%)	
	Romany/Other	34 (19.2%)	12 (13.5%)	12 (33.3%)	12 (25%)	0.033
Social support	High social support	44 (25.1%)	23 (25.6%)	2 (5.4%)	19 (39.6%)	
	Low social support	131 (74.9%)	67 (74.4%)	35 (94.6%)	29 (60.4%)	0.002
		**All participants Mean (SD)**	**Control group Mean (SD)**	**Intervention A Mean (SD)**	**Intervention B Mean (SD)**	**p**
Children		3.23 (2.16)	2.96 (3.33)	3.22 (3.69)	3.75 (2.16)	0.171
Age		61.66 (12.47)	62.37 (11.46)	60 (12.28)	61.59 (14.35)	0.721
HbA1c		8.77 (1.46)	8.57 (1.37)	8.74 (1.57)	9.16 (1.50)	0.031
Systolic pressure		130.63 (16.56)	127.90 (15.19)	128.43 (15.65)	137.16 (18.03)	0.004
Diastolic pressure		76.47 (11.32)	75.61 (9.41)	75.22 (11.04)	78.94 (14.18)	0.028
Abdominal circumference		107.44 (11.39)	105.73 (11.63)		111.16 (10.09)	0.030
HDL		47.64 (15.83)	48.66 (15.14)	46.43 (18.32)	46.64 (15.27)	0.378
LDL		122.82 (36.52)	125.40 (36.37)	120.64 (43.65)	119.56 (30.75)	0.453
Triglycerides		208.91 (165.13)	186.94 (89.40)	250.27 (258.79)	218.11 (179.53)	0.853
Body mass index		32.60 (5.72)	31.64 (5.40)	34.47 (5.50)	33.25 (6.17)	0.023

The sample is composed by a greater proportion of female patients (54.3%). The mean age of the sample is 61.99 years. Patients have an average of 3.23 children, and there are no significant between-group differences in these variables. Furthermore, 80.8% of the sample is Caucasian. A smaller proportion of this ethnicity is found in intervention group A (*p* = 0.033). Social support is low in the majority of the sample (74.9%), and the group B has a higher percentage of high social support (*p* = 0.002).

During the recruitment phase, one of the GPs did not arrange 14-day follow-up appointments for patients as stipulated in the study design. As a result, the baseline patient data used was from just 8 of the 9 GPs at the health centre. Although we considered replacing this GP, who declined to take part, with another similar one, in the end we could not do this for practical reasons.

Observed mean HbA1c value was 8.77%. For the control group this value was 8.57%, for intervention A it was 8.74% and for intervention B it was 9.16% (*p* = 0.031). For the lipid profile, the mean values of LDL, HDL and triglycerides were 122.82 mg/dL, 47.64 mg/dL and 208.91 mg/dL, respectively. There were no differences between the three groups. The mean systolic pressure was 130.63 mmHg (CG: 127.90; IA: 128.43 and IB: 137.16). The mean diastolic pressure was 74.47 mmHg (CG: 75.61; IA: 75.33 and IB: 78.94), with a significantly higher mean value in intervention group B. Likewise, significant differences were observed in the mean values of Body Mass Index, with 31.64, 34.47 and 33.25 kg/m2 being the mean values for the control group, intervention A and intervention B, respectively (*p* = 0.023).

## Discussion

This study has examined an intervention designed to improve self-management of diabetes in a group of patients with a low level of education. It describes the process, the results of the recruitment phase and the sample group’s baseline characteristics.

The sociodemographic profile of the patients in this study is similar to that of previous studies: a high percentage of patients in the group were women, from minority ethnic groups, and with little social support. The higher number of women in the group is consistent with the findings of other studies [14,20] despite the fact that T2DM is more prevalent amongst men. This may be because HbA1c levels are worse amongst women because they do not manage the disease as well, as found in other studies [21-24], or because women attend primary care appointments more frequently [25-27]. Furthermore, although only one study criterion related to social inequalities was used (level of education), the majority of the group was made up of women, ethnic minorities and people with little social support. This shows that social inequalities are often closely interlinked, making life even harder for these patients.

With regard to the clinical profile of patients in the study group, it is important to note that their test results were very high, higher than the recommended levels [28]. This is consistent with the literature on inequalities and with other interventions in disadvantaged groups and patients with diabetes [29-32]. We should also point out, however, that most of the test results were much more moderate in the control group than in the intervention groups. Because the sampling was done precisely, these differences will be taken into account in future analyses.

In order to carry out this study and choose the intervention type used, the authors carried out a systematic literature review of healthcare interventions that aim to improve diabetes care in socially vulnerable groups, identifying a total of 101 interventions (pending publication). Over recent years, a large number of interventions have been carried out in order to improve self-management of diabetes, and interventions aimed at socially disadvantaged groups have been found to be effective [10-12]. However, most of the interventions were carried out in the United States, a country with a healthcare system that does not offer healthcare services to the entire population. This is the first intervention in Spain specifically aimed at a diabetic population with a low level of education, and one of the few studies conducted in European countries. This study will provide new information about how to encourage satisfactory self-management of diabetes in a particularly vulnerable group, improving quality of care, quality of life and life expectancy, and reducing inequalities in diabetes care.

The study’s viability and methodological rigour were guaranteed because the intervention was planned by a multidisciplinary group of public health professionals with a good understanding of the methodological aspects of a study of this type. Furthermore, the study was carried out by primary care professionals with a good knowledge of the characteristics and habits of the reference population.

Another of the intervention’s strong points is its low cost. This is especially important today given the financial crisis and austerity measures affecting social welfare [33,34]. The intervention could also be easily transferred to other areas of the primary care system, which is the perfect setting given the high level of effectiveness of the intervention found in previous studies. In countries like Spain, which has its own national public health system, primary care is usually the first point of call for patients looking for healthcare services, and it has the potential to help reduce social inequalities in health [35,36]. T2DM is a very important disease because of its prevalence and cost, and although there are primary care guidelines in place, the results are not always satisfactory because effective management of the disease is hampered by difficulties [37]. Finally, the effectiveness of telephone reinforcement in interventions aiming to change patient behaviour has been widely proven. This technique is also very practical, because the patients do not need to attend the centre itself and telephones are widely available in primary care facilities [30,38,39].

There were a number of limitations to the study. Firstly, it was difficult to achieve the estimated sample size, and this could limit the statistical power to detect differences between the groups and the loss of patients during the follow-up period. Furthermore, this type of design may also be affected by bias in the standardisation of interventions. However, the professionals in charge of carrying out the two interventions were provided with training so that their interview styles would be as similar as possible, and joint meetings were organised in order to standardise the two intervention types as much as possible (in terms of intervention duration, empathy, emphasis and use of other communication skills). All of the doctors who took part in the study worked in the same health centre, so it was possible to standardise the population group.

The main intervention was carried out by healthcare staff during patients’ usual appointments, so the participation rate was high. The intervention was also designed to be as simple as possible in order to minimise the amount of work required from the doctors taking part. However, although the intervention was well-received by medical staff, the recruitment process was slower than anticipated, so the recruitment phase was extended to 5 months so that enough patients could be recruited for each group. Furthermore, there were recruitment problems during the initial stages with one of the GPs, and no other reason for this was found apart from the usual workload pressure. This shows that in order for healthcare staff to be able to devote extra time to carrying out studies of this type, it would be a good idea to combine the research work with their normal patient appointments. Additionally, consultation of the patients’ computerised clinical histories revealed an estimated prevalence of diabetes of approximately 900 patients, an average of 100 patients per GP, enough for the desired sample group size. Although the GPs were randomised, the patients who met the inclusion criteria were not evenly distributed across the different GPs, especially in terms of their level of education. Finally, a large number of patients left the study between the first and second appointments.
